##### RAPICE stage 3: MBC assessment protocol adaptation and site selection

After consensus has been achieved regarding core themes from RAPICE Stages 1 and 2, the MBC assessment protocol will be adapted. Measure adaptation will likely include modifications to the MBC content including addition of new questions, revision of question wording, and modification or addition of follow up probing questions. Researchers and community partners will also review mixed methods data to inform how frequently (i.e. weekly, biweekly) counselors will deliver MBC with patients, and how often implementation support (i.e., supervision) will be provided. This process will result in the establishment of an MBC assessment protocol that will delineate methods for its administration in group counseling sessions, documentation in the health record, and supervision procedures [31]. The adapted MBC assessment protocol will be used for implementation of the pilot trial.

The final step of the RAPICE methodology will be the selection of OTPs for the Phase 2 pilot MBC trial [57]. Researchers and community partners will review the RAPICE qualitative data along with average site scores on the quantitative surveys. Researchers will then select the four OTPs with the highest implementation potential for Phase 2 participation (i.e. highest ratings of attitudes about MBC, readiness to change, organizational climate, and workflow facilitative of MBC integration) [57].

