##### MBC integration

Informed by existing OTP workflow and health record documentation data gathered via RAPICE, researchers will meet with relevant leaders and information technology specialists at each of the OTPs to integrate the adapted MBC protocol into the workflow. Similar to Phase 1, each OTP will sign an Organization Participation Agreement outlining Phase 2 activities that will include an agreement to make electronic medical record changes to integrate MBC and extract de-identified data. At the beginning of the integration process, researchers will complete a second round of clinic site visits focused on integration of MBC into both group counseling and documentation procedures using collaborative research design principles [59–61]. The collaborative design approach will include meetings with leaders, counselors, and associated information technology specialists at each site to evaluate MBC documentation needs. OTPs provide a wide range of group counseling services covering numerous topics (e.g. recovery support, Cognitive Behavioral Therapy), and we anticipate that some patients may attend multiple groups each week. As a result, collaborative meetings will also focus on identifying which groups would be most appropriate for MBC integration. Informed consent will be obtained from all leaders and counselors participating in integration meetings. Up to 40 (approximately 8 to 10 per site) participants will be invited to contribute to meetings, each of which will be will be compensated $50.

The multi-site OTP organizations participating in this study use electronic medical record systems that can be modified by adding new templates, checklists, and/or dot phrases to facilitate documentation. Investigators will meet with appropriate health data specialists to determine an MBC documentation plan, which will be followed by changes to the electronic medical record interface based on feasibility and counselor needs. These electronic medical record changes may vary from a full, automated integration of MBC into provider documentation to the addition of simple dot phrases or note templates. Meetings with health data specialists will also involve development of methods for the OTPs to extract fully deidentified MBC outcome data from the electronic medical record [59, 61].

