Patient opioid abstinence: The secondary MBC effectiveness outcome measure is patient opioid abstinence. The same charts extracted for treatment engagement will also be reviewed for opioid abstinence. Charts will be reviewed to identify the proportion of negative opioid urine screens for each patient monthly across 6 months prior to and post MBC integration. We anticipate that some patients in our chart sample will discontinue treatment (e.g. due to discharge or leaving the OTP) during the 6 months prior to and post MBC integration. For patients who discontinue treatment, opioid abstinence will be calculated as the proportion of negative urine screens for each month that they were present in the program. We will include an indicator in the data set to denote that urine drug screen data was unavailable for the months following patient treatment discontinuation.

Counselor MBC exposure: The primary MBC implementation outcome measure is monthly counselor MBC exposure. Counselor-level exposure refers to the number of group counseling sessions each month where MBC was administered divided by the total number of group sessions completed each month by OTP counselors (i.e. total opportunities to use MBC) [62]. The total number and dates of monthly completed group counseling sessions delivered by counselors who attended the MBC workshop. will be extracted from the EMR at all four sites. Documentation from each of these counseling sessions will be reviewed to determine whether or not MBC was recorded. Monthly MBC exposure values will be computed by dividing the total number of sessions with MBC documentation by the total number of sessions completed across each of the 6 months post MBC integration.

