Counselor MBC fidelity: The secondary MBC implementation outcome measure is monthly counselor MBC fidelity. Counselor MBC fidelity refers to the degree to which counselors use MBC according to the established protocol (i.e. administering the questions, reviewing responses, discussing responses with patients in group counseling). Fidelity data will be computed as a categorical variable for completed group counseling sessions delivered by counselors who attended the MBC workshop across 6 months post integration. Counselors will receive a “1” if they documented MBC administration, a “2” if they documented administration and response review or administration and MBC discussion, and a “3” if they documented administration, response review, and MBC discussion with the patient. All attended counseling sessions without MBC documentation will receive a “0” [19].

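### The denominator of the primary implementation outcome, and the fidelity score of 0, take in group sessions where MBC may never have been intended, so full adherence can score below 100%

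*Protocol article*

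**What the plan says.** All references are to the Protocol article.

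- **Measures, counselor exposure.** "The primary MBC implementation outcome measure is monthly counselor MBC exposure". It is the count of group sessions with MBC "divided by the total number of group sessions completed each month by OTP counselors (i.e. total opportunities to use MBC"). The sessions to be extracted are described as "The total number and dates of monthly completed group counseling sessions delivered by counselors who attended the MBC workshop", and the monthly value comes from "dividing the total number of sessions with MBC documentation by the total number of sessions completed across each of the 6 months post MBC integration". None of these sentences limits the sessions to groups chosen for MBC.
- **Measures, counselor fidelity.** Fidelity is the degree to which MBC is used as the protocol lays down, scored 1 to 3 by the steps documented. "All attended counseling sessions without MBC documentation will receive a" score of 0. No exemption is made for groups that were not chosen.
- **MBC integration.** The programs run many kinds of groups and some patients may attend several a week. For that reason, "collaborative meetings will also focus on identifying which groups would be most appropriate for MBC integration".
- **RAPICE stage 3.** Phase 1 data are to inform "how frequently (i.e. weekly, biweekly) counselors will deliver MBC with patients".
- **MBC delivery.** The anticipated process, subject to adaptation, has the counselor give the questions at the start of every group session. The Introduction describes delivery with fidelity in similar terms.

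**The concern.** The exposure definition treats completed group sessions and opportunities to use MBC as the same set. The integration plan separates them: if only some groups are chosen, sessions of the others are not opportunities. A counselor who correctly leaves MBC out of an unchosen group is following the protocol, yet loses exposure and receives the lowest fidelity score for that session.

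The shortfall need not be the same everywhere. Integration is planned with each program, so the share of sessions designated can vary by site and, within a site, by which groups a counselor leads. The scores would then mix two things: how many groups were designated, and what counselors did in them. The multilevel models planned under outcome data analysis take exposure and fidelity as outcomes, with counselor-level and program-level predictors. They also use fidelity to explain engagement and abstinence, which is Hypothesis 3. With four sites, differences in designation could not be reliably separated from program-level predictors such as implementation climate.

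**Working it through.** The protocol states no target, expected value or cut-off for exposure, so there is no figure to reproduce. The check is what the stated rule yields when counselors do everything asked of them.

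**Inputs**

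- Numerator: sessions with MBC documented (Measures).
- Denominator: all completed group sessions of workshop-trained counselors (Measures).
- *s*, the share of a trained counselor's group sessions that belong to groups chosen for MBC. Not given; taken here as 0.25 to 1.00 (assumption).
- *f*, the share of those sessions at which MBC is due. It is 1 if due at every session, as MBC delivery anticipates. For a weekly group it is 0.5 if the second option in RAPICE stage 3 means every other week (assumption, since that word can also mean twice a week).

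**Formula.** Exposure under perfect delivery = *s* × *f*.

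| *s* | due at every session (*f* = 1) | due every other week (*f* = 0.5) |
|---|---|---|
| 1.00 | 100% | 50% |
| 0.75 | 75% | 37.5% |
| 0.50 | 50% | 25% |
| 0.25 | 25% | 12.5% |

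**Worked case (assumed caseload).** A counselor runs 4 weekly groups for 4 weeks: 4 × 4 = 16 sessions. MBC is placed in 2 of the groups.

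- Due every week: 2 × 4 = 8 sessions with MBC. As written, 8/16 = 50%. With only due sessions in the denominator, 8/8 = 100%.
- Due every other week: 2 × 2 = 4 sessions with MBC. As written, 4/16 = 25%. With only due sessions, 4/4 = 100%.

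**Fidelity.** If each due session scores the full 3, all others score 0 and scores are averaged over sessions, the mean is 3 × *s* × *f*: 3 × 0.50 = 1.5 at a 50% ceiling and 3 × 0.25 = 0.75 at a 25% ceiling.

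**Between sites.** With *f* = 1, two sites whose counselors all deliver perfectly, one with *s* = 1.00 and the other with *s* = 0.50, would differ by 100 − 50 = 50 percentage points.

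The group-selection part does not depend on *f*: the middle column falls below 100% as soon as *s* is below 1.

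**The case against.** The case on the other side is substantial, and part of it stands.

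- **The shortfall is conditional.** The protocol does not say that trained counselors will also run unchosen groups, or how many. Data are extracted only for counselors who completed the workshop; if they lead mainly chosen groups, the ceiling approaches 100%. This stands. A reader might infer from the table that exposure will be capped at 25% to 50%, but those values need an assumed half-designation, or every-other-week delivery, or both.
- **Frequency is the weaker strand.** The Introduction and MBC delivery both describe MBC at each session; RAPICE stage 3 only lists options for Phase 1 to inform. This also stands, and the right-hand column applies only if an every-other-week schedule is adopted.
- **Low exposure need not be taken as failure.** A reader might infer that it would be, but no threshold exists. The criterion for a larger trial, under Sample size and power considerations, is an effect on engagement or abstinence together with acceptability and feasibility evidence from Phase 1. The Discussion says only, in qualitative terms, that significant implementation challenges would redirect later work. A low score could feed that judgement; nothing makes it decisive.
- **The effectiveness results are untouched.** The pre-post *t*-tests use neither exposure nor fidelity, and the models that do are labelled exploratory.
- **An all-session denominator is a legitimate measure.** It shows how far MBC has entered a counselor's group work, and sessions without MBC gave patients none whatever the reason. That is a good reason to keep it as reach. It does not rescue the present definition, which claims to count opportunities.
- **Phase 2 details depend on Phase 1.** True, but the denominator is not a detail left open: it is stated and repeated, and would be applied as written unless changed.

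**Conclusion.** The point holds as an inconsistency between a fixed rule and the planned intervention. Exposure equates all completed sessions of trained counselors with opportunities, and fidelity scores undocumented sessions 0, while the integration plan allows some groups to carry no MBC. Wherever a trained counselor runs such groups, perfect delivery scores below 100%, with a ceiling of *s* × *f*. For illustration this is 50% if half the sessions are designated and MBC is due at each of them. Over the assumed ranges the ceiling runs from 12.5% to 100%, and the upper end, no distortion, is compatible with the text.

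The consequence is possible understatement of the primary and secondary implementation outcomes, by an amount that may vary with counselor and site, and possible confounding of the exploratory models, including the one bearing on Hypothesis 3. The documents do not support calling the bias certain, attaching a definite percentage to it, or saying that the trial would be declared a failure because of it. It should be corrected before Phase 2 data are extracted.

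**What to change.** 1. Define the exposure denominator as completed sessions, led by workshop-trained counselors, of MBC-designated groups at which MBC is due under the adopted schedule. Restrict the numerator to the same sessions.
2. Apply the fidelity score of 0 only within that set. Sessions outside it receive no fidelity score.
3. Report the all-session proportion separately as reach, with the share of groups designated, by site.
4. Reconcile RAPICE stage 3 with MBC delivery on how often MBC is given, so that a due session is defined once. Which schedule to adopt is for the investigators.

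Perfect delivery then scores 100% for any number of designated groups and any schedule. The cost is a designation flag in the electronic record extract, drawn up once the integration meetings have identified the groups, and a few sentences of protocol text. One drawback remains: a site that designates very few groups could score high on exposure. The reach figure would show this, so the two should be presented together.

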##### MBC effectiveness and implementation outcome data analysis

Descriptive statistics will be explored (means, standard deviations, ranges) for all outcome variables to determine preliminary MBC effectiveness and implementation across all sites. Mean comparisons will test MBC effectiveness and implementation hypotheses. Specifically, *t*-tests will be conducted to compare average pre- and post-MBC treatment engagement proportions/number of weeks of MOUD and counseling attended and opioid abstinence proportions.

Additional exploratory analyses will employ Multi-Level Modeling to identify the impact of MBC fidelity on patient treatment engagement/abstinence as well as predictors of MBC exposure and fidelity at both the individual counselor and OTP level while accounting for data nested within OTPs. Predictors of patient treatment engagement/abstinence to be explored include biological sex, gender identity, age, race, ethnicity, prior MOUD receipt at the OTP, MOUD type and dose, and number of co-occurring disorders. Predictors of MBC exposure and fidelity to be explored at the counselor level include biological sex, gender identity, age, race, ethnicity, years employed at the OTP, and attitudes toward MBC. Predictors to be explored at the OTP level include organizational functioning and implementation climate (measured in Phase 1; see Phase 1 Quantitative Surveys). Missing data will be analyzed to evaluate percent missingness, and analyses will employ multiple imputation methods in the event of substantial missing data.

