#### Phase 2: pilot MBC hybrid effectiveness implementation trial

The objective of Phase 2 is to evaluate the effectiveness and implementation potential of MBC via a pilot hybrid type 1 MBC effectiveness-implementation trial with four OTPs. This phase will last approximately 33 months. Although MBC has extensive evidence in mental health and some substance use settings, evidence is limited in OTPs. Thus, consistent with best practices in a Type I hybrid effectiveness-implementation trials [58], this pilot study will prioritize data on effectiveness while simultaneously gathering implementation data.

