##### Measures

All effectiveness and implementation outcome data collected in Phase 2 will be fully deidentified data extracted from the medical record. Counselor data will only be extracted for those who completed the MBC workshop, whereas patient data will only be extracted for those treated by counselors who completed the workshop. Patient treatment engagement data and opioid abstinence will be collected monthly across 6 months prior to and post MBC integration to evaluate preliminary effectiveness and implementation. Counselor MBC exposure and fidelity will be assessed post MBC integration only. Demographic data will also be extracted for all counselors and patients (e.g. age, biological sex, race, ethnicity). Finally, information about prior treatment at the OTP (i.e. patients who received care previously but came in again as new patients), patient MOUD type and dose, and patient DSM diagnoses (including other substance use or mental health disorders) will be extracted.

Patient treatment engagement: The primary MBC effectiveness outcome measure is patient treatment engagement, which we have broadly defined to encompass both completion of methadone/buprenorphine dosing visits and attendance at counseling/psychosocial intervention appointments. Approximately 20 charts per site (*N* = 80) will be randomly selected from new patients that entered treatment over the 6 months prior to MBC integration. An additional separate set of 20 new patient charts per site (*N* = 80) will be extracted to evaluate treatment engagement in the 6 months following integration. Charts will be reviewed to identify the proportion of treatment visits attended (i.e. MOUD dosing visits and individual/group counseling appointments) out of total visits scheduled for each patient, as well as the total number of weeks each patient was retained in treatment.

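### The pre/post effectiveness tests are unadjusted t-tests on two non-randomised patient sets, so measured case-mix shifts enter the effect size that decides and sizes the next trial

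*Protocol article*

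**What the plan says.** The Measures section of Phase 2 defines two chart samples. The earlier one, about 20 charts per site, "will be randomly selected from new patients that entered treatment over the 6 months prior to MBC integration". The later one is "An additional separate set of 20 new patient charts per site". Phase 2 is a "pilot hybrid type 1 MBC effectiveness-implementation trial with four OTPs", so there are 80 patients on each side, nobody is in both sets, and each site supplies equal numbers to both periods.

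The same section plans to collect patient characteristics: "Demographic data will also be extracted for all counselors and patients (e.g. age, biological sex, race, ethnicity"), then "information about prior treatment at the OTP", medication type and dose, and diagnoses.

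The outcome data analysis section says: "Mean comparisons will test MBC effectiveness and implementation hypotheses". The named method is t-tests that "will be conducted to compare average pre- and post-MBC treatment engagement proportions/number of weeks of MOUD and counseling attended and opioid abstinence proportions". No site term or covariate is attached to them. Multilevel models "while accounting for data nested within OTPs" follow as additional exploratory analyses. They are directed at fidelity and at predictors of engagement, abstinence, exposure and fidelity, not at the pre/post contrast.

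Sample size and power considerations gives a detectable effect of 0.39 for 80 charts before and 80 after. It treats a small to medium effect on either outcome, together with acceptability and feasibility, as preliminary support for a larger trial. The effect found is then to be used to size that trial.

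**The concern.** Without randomisation, the difference between the two means combines any MBC effect with any difference in who entered treatment in each window. The plan intends to collect factors that could explain part of that difference, and it names them as candidate predictors of the same outcomes, yet the effectiveness estimate uses none of them.

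The estimate matters more than the p-value here, because it feeds the decision on a larger trial and the size of that trial. A raw difference that partly reflects patient mix carries its bias into both.

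A second, smaller issue is the standard error. Charts are drawn by site, but the t-test treats 80 and 80 as simple random samples.

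**Working it through.** **Inputs.** From the documents: four sites, 20 charts per site per period, 80 per group, stated detectable effect 0.39, and 484 patients for a future trial at d = 0.3. Assumed, because the documents give no values: the size of case-mix shifts, the prognostic strength of the factor, the intraclass correlation ρ, and the share c of site variance that is stable across periods. Outcomes are scaled to SD = 1.

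**Reproducing 0.39.** Two independent groups, no site or covariate term: SE = √(2/80) = 0.158. With one-sided 5% and 80% power, detectable d = (1.645 + 0.842) × 0.158 = 0.393 (0.395 with the t distribution). Two-sided 5% and 80% power gives 0.443 (0.446 with t). The stated figure therefore fits a plain two-sample comparison, most likely one-sided; alpha, sidedness and power are not given.

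**Case mix.** Bias = (shift in prevalence between periods) × (outcome difference for that factor, in SD).

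| Shift | Factor effect (SD) | Bias in d | Share of 0.39 |
|---|---|---|---|
| 0.10 | 0.3 | 0.030 | 8% |
| 0.15 | 0.5 | 0.075 | 19% |
| 0.20 | 0.8 | 0.160 | 41% |

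The bias can have either sign. Its effect on sizing follows from N being proportional to 1/d². If the true effect were 0.30 (N = 484), an estimate of 0.375 would give 484 × (0.30/0.375)² ≈ 310. An estimate of 0.225 would give 484 × (0.30/0.225)² ≈ 860.

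**Standard error.** With ρ and c as above:

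- True variance of the difference = 2 × [(1 − ρ)/80 + ρ(1 − c)/4].
- Expected variance used by the t-test = (2/80) × [(1 − ρ) + ρ × 60/79].

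Example, ρ = 0.05. The t-test variance is (2/80) × (0.95 + 0.038) = 0.0247, SE 0.157. With c = 1 the true variance is 2 × 0.95/80 = 0.02375, SE 0.154, ratio 0.98. With c = 0.5 it is 2 × (0.95/80 + 0.025/4) = 0.03625, SE 0.190, ratio 1.21.

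| True SE / t-test SE | ρ = 0.02 | ρ = 0.05 | ρ = 0.10 |
|---|---|---|---|
| c = 1 (site differences stable) | 0.99 | 0.98 | 0.96 |
| c = 0.8 | 1.03 | 1.08 | 1.15 |
| c = 0.5 | 1.09 | 1.21 | 1.40 |

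The ratio falls on either side of 1 according to c, which the documents do not give.

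**The case against.** **Pilot status and acknowledged limits.** The Discussion concedes limited power and the absence of a concurrent comparison. Progression rests on effect size plus acceptability and feasibility, not on significance. This stands as far as it goes, but it makes an unadjusted effect size more of a problem, not less, and neither concession mentions patient mix.

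**Comparability is partly protected.** Both sets come from the same four sites, are new patients, and were treated by counselors who completed the workshop. That limits the likely shift without ruling it out. The shifts used above are illustrations.

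**The p-values must be too small.** A reader might infer this from the ignored site structure. The documents do not support it. Every site contributes to both periods, so stable site differences make the t-test slightly conservative. Understatement requires a pre/post change that differs by site or counselor. Moreover, the four sites are chosen for high implementation potential; if inference is meant for those four only, site-specific responses are part of the average effect rather than error.

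**The plan ignores site and baseline data altogether.** A reader might infer this too. It is true only of the pre/post contrast. Hypothesis 3, on fidelity, has a nested model, and the patient factors are to be explored as predictors. Those data are planned for extraction; Phase 1 is only starting.

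**Details may sit in the full protocol.** Possibly, for sensitivity analyses. But the article itself names the t-test as the test of the effectiveness hypotheses.

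**Conclusion.** The point holds for hypotheses 1 and 2. The effectiveness estimate is a raw difference between non-randomised patient sets, although site and several prognostic factors will be available. Under the assumed shifts, a single factor moves d by 0.03 to 0.16, or 8% to 41% of the stated 0.39, in either direction.

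The standard error does not match the sampling, but neither the direction nor the size of the mismatch can be derived from the documents. Over ρ from 0.02 to 0.10 and c from 0.5 to 1, the correct value is 0.96 to 1.40 times the t-test value. No claim of an inflated error rate should be drawn from this.

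Nor should a reader conclude that adjustment would make the design equivalent to a concurrent comparison. It deals with measured patient mix only.

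**What to change.** Make the main analysis of each pre/post outcome a regression with period, site as a fixed effect, and a short prespecified list of covariates fixed at induction: age, sex, prior treatment at the OTP, medication type at induction, and diagnoses only as recorded at intake. Leave out anything that can change after MBC starts. Carry the adjusted period effect forward to the decision on, and sizing of, the next trial.

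Report the four site-specific differences, or a site-by-period term, so that heterogeneity is visible. A site fixed effect alone does not absorb such variation. Each site difference has SE √(2/20) = 0.32 SD, so these are for display, not for testing. Keep the t-test as a descriptive supplement.

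Allow for counselor clustering only if a patient-counselor link can be extracted, with a small-sample correction. The Measures section does not list such a link, and the protocol expects some patients to attend several groups. State that adjustment leaves calendar-time confounding in place.

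The cost is wording, minor extra analysis, and a few degrees of freedom out of 160 charts (three for site, about one per covariate). The characteristics are already on the extraction list; what must be added is that medication type and diagnoses are taken as of induction or intake.

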The Measurement-Based Care to Opioid Treatment Programs (MBC2OTP) Project addresses the need to advance the uptake of MBC in OTPs via three specific aims. Aim 1 is to inform MBC implementation via a novel mixed methods approach, Rapid Assessment Procedure Informed Clinical Ethnography (RAPICE) [42]. RAPICE embeds participant observation within front-line study team members and treatment providers engaged in rolling-out clinical procedures, combined with regular data review/analyses with an implementation science mixed methods expert consultant [42]. Aim 2 is to apply the RAPICE mixed-methods results to adapt an MBC assessment protocol for OTP use. Aim 3 is to simultaneously evaluate both effectiveness and implementation outcomes via a hybrid type 1 effectiveness-implementation trial. No a priori hypotheses were developed for Aims 1 and 2 given their exploratory nature and focus on development of an MBC protocol. Aim 3 will test the following hypotheses: (1)* Treatment engagement will increase across all sites following MBC electronic medical record integration*; (2) *Negative opioid urine screens will increase across all sites following MBC electronic medical record integration*; (3)* The extent to which counselors deliver MBC with fidelity will be positively associated with patient engagement in treatment sessions (both medication dosing and counseling appointments) and patient opioid abstinence across all sites.*

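### The exploratory multilevel models regress on OTP-level predictors with only four selected OTPs, and name no nesting within counselor

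*Protocol article*

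**What the plan says.** Phase 2 is described as a "pilot hybrid type 1 MBC effectiveness-implementation trial with four OTPs". On how those sites are chosen, the section on RAPICE stage 3 says: "Researchers will then select the four OTPs with the highest implementation potential for Phase 2 participation". Organizational climate is one of the listed criteria, judged together with each site's average Phase 1 survey scores. The Implementation Climate Scale is part of that survey (RAPICE stage 1: quantitative surveys).

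The section on MBC effectiveness and implementation outcome data analysis labels the multilevel models exploratory. They have two uses: relating MBC fidelity to patient engagement and abstinence, and finding "predictors of MBC exposure and fidelity at both the individual counselor and OTP level while accounting for data nested within OTPs". At counselor level the candidates are "biological sex, gender identity, age, race, ethnicity, years employed at the OTP, and attitudes toward MBC". At site level, "Predictors to be explored at the OTP level include organizational functioning and implementation climate".

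Under Measures, exposure is a monthly proportion over the six months after integration. Fidelity is called monthly but is scored 0 to 3 for completed group sessions. Session counts and dates "will be extracted from the EMR at all four sites".

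Among the Aim 3 hypotheses at the end of the introduction, the third is: "The extent to which counselors deliver MBC with fidelity will be positively associated with patient engagement in treatment sessions". It extends to opioid abstinence.

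**The concern.** There are two separate matters.

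**Site-level predictors.** A coefficient for an OTP characteristic is informed by the number of OTPs, not by the number of sessions, counselors or charts. Four sites give very little to work with, and choosing the top four of eight partly on climate narrows the spread of one of the predictors. This is fixed by the design; no later analysis wording can add sites.

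**Counselor nesting.** Each counselor contributes repeated exposure and fidelity values, and seven of the named predictors vary only between counselors. If the model clusters on OTP alone, repeated values from one counselor count as independent and the standard errors are too small. This reaches a named hypothesis. The pre/post t-tests cannot address hypothesis 3, because fidelity exists only after integration, so the multilevel model is the only described analysis that can. Its predictor is a counselor behaviour, shared by patients of the same counselor.

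**Working it through.** The article gives no figure for these models. Its one detectable effect (0.39 with 160 charts) concerns the pre/post comparison and has no bearing here.

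**1. Site-level predictors.** Input: 4 OTPs. Residual df = 4 − 1 − p for p site-level predictors. The smallest |r| (partial |r| when p = 2) giving two-sided p<0.05 is t/√(t² + df).

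- p = 1: df = 2, t = 4.303, |r| = 4.303/√(18.51 + 2) = 0.95.
- p = 2: df = 1, t = 12.706, partial |r| = 12.706/√(161.4 + 1) = 0.997.

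Simulated power with one predictor is about 10% at a true site-level correlation of 0.5 and 25% at 0.8.

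If software uses a normal reference (critical value 1.96) on four site means, the type I error is P(|t| > 1.96) on the true df:

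- 2 df: 1 − 1.96/√(1.96² + 2) = 0.19.
- 1 df: 1 − (2/π)·arctan(1.96) = 0.30.

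**2. Random OTP variance.** Suppose the four site means were known without error and normally distributed. The variance estimate would have 3 df, and its 95% interval would run from 3/9.35 = 0.32 to 3/0.216 = 13.9 times the estimate.

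**3. Counselor level, if omitted.** For a predictor constant within counselor, the design effect is 1 + (m − 1)·ICC, where m is the number of values per counselor. The standard error is understated by its square root. The article supplies m = 6 for monthly values. The ICCs, the session counts and the number of counselors are assumptions.

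| Data | m | ICC | Design effect | SE factor |
|---|---|---|---|---|
| Monthly | 6 | 0.1 | 1.5 | 1.22 |
| Monthly | 6 | 0.3 | 2.5 | 1.58 |
| Session (assumed count) | 24 | 0.1 | 3.3 | 1.82 |
| Session (assumed count) | 48 | 0.3 | 15.1 | 3.89 |

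A simulation with 4 sites, 4 to 10 counselors per site and six monthly values, with site differences removed, agrees. The factor is about 1.2 at ICC 0.1 and 1.6 at ICC 0.3. Type I error is about 11% and 22–23% without a counselor level, and 4–5% with it.

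**4. Hypothesis 3.** Outcomes come from about 20 post-integration charts per site (80 in all). With the same assumed 4 to 10 counselors per site, that is 20/10 = 2 to 20/4 = 5 charts per counselor. Taking one value per chart:

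- m = 2, ICC 0.1: √(1 + 1 × 0.1) = 1.05.
- m = 5, ICC 0.3: √(1 + 4 × 0.3) = 1.48.

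This is smaller than for the monthly exposure and fidelity models.

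**The case against.** - **The models are labelled exploratory, and the Discussion concedes limited power.** Both are true and lower the severity. But the concession concerns pilot power in general and does not mention the four-site limit. Hypothesis 3 is also listed among those Aim 3 will test.
- **The two site-level predictors may be tried one at a time.** The text does not say they enter together, so the 1-df case is conditional. One at a time still leaves only 2 df.
- **The text does not say that OTP is the only random effect.** It plans predictors "at both the individual counselor and OTP level while accounting for data nested within OTPs", which names the counselor as a level. A condensed article commonly leaves the random-effects structure to a fuller document. This stands: the counselor part is a request to state the structure, not proof of a wrong model.
- **Patients may attend several groups**, so simple nesting of patients within one counselor may not hold. This also stands and is allowed for in the fix.

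Three stronger readings are tempting but unsupported. A reader might infer that site effects cannot be estimated at all; one or two slopes are computable, but uninformative. A reader might infer that counselor-level standard errors are certainly far too small, by about 1.8 to 4 times. That needs both an omitted counselor term and session-level data at assumed counts. A reader might infer that these coefficients will steer the next trial. The sample size section ties support for a larger trial to the engagement or abstinence effect size plus Phase 1 acceptability and feasibility.

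**Conclusion.** The point holds in two parts of different strength.

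The site-level part is firm, because it rests only on the stated four OTPs. With 2 or 1 residual df, coefficients for organizational functioning and implementation climate, and a random OTP variance, cannot be estimated with useful precision. A large-sample reference would make chance findings common. Selection partly on climate makes matters worse by an amount the article does not let one calculate.

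The counselor part is conditional. If no counselor term is fitted, standard errors for counselor-level predictors are understated about 1.2- to 1.6-fold on six monthly values at ICCs of 0.1 to 0.3. The understatement is more on session-level scores and less in the 80-chart hypothesis 3 model. The article gives no ICC, counselor count or session count, so these sizes are a range under assumptions.

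The primary pre/post comparison is not affected by this point. The plan should be amended, but the exploratory label keeps this below a critical fault.

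**What to change.** - Report organizational functioning and implementation climate descriptively by site, beside each site's exposure and fidelity, and drop them as OTP-level regressors.
- Fit OTP as a fixed effect. Measures constant within a site are then collinear with it, so this goes together with the first change.
- State a counselor random intercept for the repeated exposure and fidelity values, and for patients in the hypothesis 3 model. Allow for patients seen by more than one counselor, for example with a multiple-membership term or a stated rule for assigning a main counselor.
- Keep a coded counselor identifier in the de-identified extract and link it to sessions and patients. Extraction methods are still to be developed with the sites, so this should be settled now; it may be hard to add later.
- Optionally, use an ordinal mixed model for the 0–3 fidelity score.

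The cost is analysis wording and one coded field. The loss is a formal test of site-level predictors, which four sites could not support anyway.
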